## 7.5 COVID-19 Case Monitoring

This clinical trial adopts a monitoring modality of positive COVID-19 cases with passive monitoring as the main approach and active monitoring as a supplement. After the participants receives the vaccination, the monitoring of positive COVID-19 cases will be initiated until the end of the study, and relevant information will be collected.

### A. Passive Monitoring

Passive monitoring has two situations where participants spontaneously report and when the participants develop any symptoms, they actively go to a hospital to seek for medical care.

1. After the participants develop symptoms, they actively report to the investigator through the hotline or email;
2. When the participants visit a hospital after developing any symptoms, the participants are monitored through hospital system;
  - When the participant has fever and/or respiratory symptoms that meet the definition of a suspected case, the participant should inform the investigator and go to the designated place for PCR testing;
  - If the participant visits a hospital for treatment, the investigator should arrange to collect nasopharyngeal swabs for PCR testing every 2-3 days; determine the clinical classification based on the severity and duration of symptoms, and isolate the mild and moderate cases; arrange hospitalization for severe and critical cases;
  - For non-hospitalized patients, the participants will be followed up by remote teleconsultation and re-tested by PCR testing every 3 days to monitor and document the progress of the illness, medication status, symptom severity and other related information. If the participant's condition deteriorates, he/she needs to be transferred to the hospital for timely treatment;
  - For hospitalized patients, continue to pay attention to the development of the disease, and conduct necessary testing and examination such as blood routine, blood chemistry, imaging examinations as well as other medical treatment. Closely monitor and collect evidence related to the participant's diagnosis and treatment, and record the progress of the disease, medication, and the severity of symptoms

CONFIDENTIAL

---

until the outcome;

- Collect the PCR result, a confirmed case is determined based on the positive result;
- During the convalescent period (defined as 3-4 weeks after the first positive PCR result) for COVID-19 infection positive participant's only, a nasopharyngeal swab is collected for PCR re-test; if the PCR test result is still positive, repeated PCR testing needs to be performed once per week until the PCR result turns negative.
- Neutralizing antibody testing will be conducted according to Investigator clinical judgement.

### **Endpoint assessment of the cases**

Establish an independent case Endpoint Assessment or Adjudication Committee (EAC) composed of 3 or more local medical experts to make a final diagnosis for each case. When a case meets the etiological indicators, the diagnosis and treatment progress document, case investigation document, serology, cytokines and other lab reports will be submitted to EAC, the case can be determined as a confirmed case of COVID-19 (clinical endpoint) after a blinded review of the EAC experts.

**Table 6 Testing for PCR positive cases in acute and convalescent phase**

|                           | Clinical Classification                 | Acute Phase                                                                              | Convalescent Phase       |
|---------------------------|------------------------------------------------|-------------------------------------------------------------------------------------------------|---------------------------------|
| PCR-positive cases | Non-hospitalized-Asymptomatic / Mild    | SARS-CoV-2 PCR testing                                                                          | SARS-CoV-2 PCR testing          |
|                           |                                                | IgM, IgG, Neutralizing antibody                                                                 | IgM, IgG, Neutralizing antibody |
|                           |                                                | Pathogenic Differential diagnosis (if applicable)                                               |                                 |
|                           | Hospitalized-Moderate/Severe / Critical | SARS-CoV-2 PCR testing                                                                          | SARS-CoV-2 PCR testing          |
|                           |                                                | IgM, IgG, Neutralizing antibody                                                                 | IgM, IgG, Neutralizing antibody |
|                           |                                                | CBC with differential (WBC, lymphocytes...)                                                     |                                 |
|                           |                                                | Blood chemistry (liver enzymes, eGFR, LDH, CRP)                                                 |                                 |
|                           |                                                | Chest CT scan/CXR                                                                               |                                 |
|                           |                                                | Pathogenic Differential diagnosis (if applicable)                                               |                                 |
|                           |                                                | Cytokines : IL-2, IL-6, IL-4, TNF- $\alpha$ , IFN- $\gamma$ and other cytokines (if applicable) |                                 |

### 7.6 Concomitant Medication

Within 0-28 days, actively follow up and observe the local and systemic adverse events of the participants and record them on the vaccination diary card. At the same time, it is necessary to record the drug used of the participants on the vaccination diary card.

**Medication Allowed:** During the clinical trial, if the participant has adverse events, necessary medication and medical treatment should be allowed.

**Vaccines Allowed:** None COVID-19 vaccines are allowed during the trial, which should be carried out 15 days after the trial vaccination. Emergency vaccination, such as rabies vaccine and tetanus vaccine, is not restricted.

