**CONFIDENTIAL**

respectively, the participants were followed-up by telephone and guided to observe the adverse events correctly and fill in the diary card.

3. On the 14th day after vaccination, the investigator reviews the filling of the diary card during this period and re-collect the diary card.
4. On the 8th -28th day after vaccination, the investigator uses telephone follow-up once a week, combined with an active report of the participants to monitor the safety.
5. When it is known that the participant has adverse reactions/events of Grade 3 or above, a face-to-face visit should take place within 24 hours.
6. SAEs and AESIs are observed from the first dose to 12 months after the full course of vaccination via monthly telephone follow-up calls and self-reports from the participants.
7. Participants should contact the doctors on informed consent form/diary card immediately if developed any COVID-19 like symptoms.

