**Blood Sample Numbering Rule**

Before the booster dose: study number – 0

14 days after vaccination (D14+10 days) study number – 1

28 days after vaccination (D28 + 10 days) study number -2

3 months after vaccination (D90 + 30 days) study number-3

6 months after vaccination (D180 + 30 days) study number -4

9 months after vaccination (D270 + 30 days) study number -5

12 months after vaccination (D360 + 30 days) study number-6

Suspected and confirmed cases are coded in P1, P2, P3...according to the order of blood collection.

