| Telephone follow-up after vaccination                                   | ✓                                                                                       | ✓                                                                                       | ✓                                                                                       |                                                                                          | ✓                                                                                          |                                                                                            | ✓                                                                                                  | ✓                                                                                                  | ✓                                                                                                  | ✓                                                                                                  | ✓                                                                                                  |                                                                                                    |                                                                                                     |

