| Concomitant Medication                                                  | ✓                                                                                       | ✓                                                                                       | ✓                                                                                       | ✓                                                                                        | ✓                                                                                          | ✓                                                                                          | ✓                                                                                                  | ✓                                                                                                  | ✓                                                                                                  | ✓                                                                                                  | ✓                                                                                                  |                                                                                                    |                                                                                                     |

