| Neutralizing Antibody/IgG Test                                          | ✓                                                                                       |                                                                                         |                                                                                         | ✓                                                                                        |                                                                                            | ✓                                                                                          |                                                                                                    | ✓                                                                                                  |                                                                                                    |                                                                                                    | ✓                                                                                                  | ✓                                                                                                  | ✓                                                                                                   |

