**CONFIDENTIAL**

1. Consent process completed, and form signed before any study-related procedures are conducted.
2. Urine/blood pregnancy test must be completed within 24 hours prior to vaccination for women of childbearing potential, and only negative test results are eligible for enrollment.
3. All participants should be observed onsite for at least 30 minutes after vaccination.
4. Paper diary cards will be used for safety information records and collected from the participant on Visit 4 (D14).
5. PCR testing could be performed any time during the study when the participant developed any suspected symptoms.
6. Collect blood samples from the first 20 participants in each study group for cellular immunity testing.

CONFIDENTIAL

CONFIDENTIAL

---

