**CONFIDENTIAL**

**Medication Record:** To understand the influence of drug use during the trial on vaccine safety and immunogenicity, and to collect adverse events that may be related to vaccination without omission, investigators should instruct the guardians of the participants to record the medical treatment and medication in diary cards as much as possible and assist in collecting the hospitalization medication records of the participants during the observation period. When SAE occurs, copies of corresponding medical records and medication records should be collected and kept. The all study additional drugs need to be transcribed into the electronic case report form (eCRF), such as but not limited to:

1. Hormone/steroid drugs and other immunosuppressants.
2. Antiallergic Drugs
3. Antipyretics/analgesics/NSAIDs
4. Prophylactic Vaccines
5. Therapeutical Medical Products
6. Antibiotics
7. Antiviral Drugs
8. Chinese Patent Drugs

CONFIDENTIAL

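### Scheduled recording of concomitant vaccines stops at month 6, but persistence blood is drawn at months 9 and 12, so an outside COVID-19 vaccine in between is captured only passively

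*Protocol*

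**What the plan says.** **Which vaccines are allowed (Protocol 7.6).** The rule reads "None COVID-19 vaccines are allowed during the trial, which should be carried out 15 days after the trial vaccination". The first word is probably a slip for *Non-*, which would make this a permission for other vaccines from day 15. Read instead as a ban, it excludes COVID-19 vaccines outright. Either way, a COVID-19 vaccine other than the trial dose is not on the allowed list.

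**What must be recorded (7.6, Medication Record).** The stated aim is to learn how drug use during the trial affects safety and immunogenicity. The duty is "The all study additional drugs need to be transcribed into the electronic case report form (eCRF), such as but not limited to", and prophylactic vaccines are item 4 of the list that follows. That sentence has no end date. The 0-28 day limit at the start of 7.6 applies to the diary card.

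**When it is recorded (Table 4 Schedule of Events).** The row "Concomitant Medication" is ticked at every visit from V1 to V11 and is blank at V12 and V13. The row "Neutralizing Antibody/IgG Test" is ticked at V1, V4, V6, V8, V11, V12 and V13. The last of these samples is defined in 7.4 as "12 months after vaccination (D360 + 30 days) study number-6".

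**What the late samples are for.** Secondary objective 2 and secondary endpoint 3 use anti-Omicron GMTs and titre proportions at 3, 6, 9 and 12 months.

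**The concern.** A further COVID-19 vaccine acts directly on the antibody titre that the persistence endpoint measures. The protocol recognises this kind of influence in 7.6, and then stops scheduled recording while half of the persistence time points are still to come. The interval matters too. The trial itself boosts people at least 6 months after their last dose, and the recording gap opens about 6 months after the trial dose. That shows when another dose becomes plausible; it is not evidence that anyone takes one.

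If such doses occur and are not recorded, the 9- and 12-month GMTs mix the persistence of the trial booster with the response to another vaccine, and the analyst cannot separate the two afterwards. Definitions and exclusions can be left to a SAP, but they can be applied only to information that was collected. Whether the participant is asked is fixed by the Schedule of Events, which is protocol content.

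**Working it through.** **1. Visits with antibody blood but no scheduled medication recording.** From Table 4:

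- Antibody visits: {1, 4, 6, 8, 11, 12, 13}
- Concomitant Medication visits: {1, 2, ..., 11}
- Difference: {12, 13}

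The persistence visits are V8, V11, V12 and V13 (months 3, 6, 9 and 12), so 2 of 4 have no scheduled recording.

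**2. Reliability of the table.** In the text as extracted, the rows for adverse events, SAEs and COVID-19 PCR each show a single tick, probably from merged cells. The Concomitant Medication row has eleven separate ticks followed by two blanks, so the same explanation is unlikely there.

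**3. Length of the gap.** The days come from the Blood Sample Numbering Rule in 7.4: month 6 = D180 + 30, month 9 = D270 + 30, month 12 = D360 + 30.

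| Interval | Nominal | Shortest | Longest |
|---|---|---|---|
| V11 to V12 | 270 − 180 = 90 days | 270 − 210 = 60 | 300 − 180 = 120 |
| V11 to V13 | 360 − 180 = 180 days | 360 − 210 = 150 | 390 − 180 = 210 |

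**4. Other routes by which a vaccine after month 6 could be found.**

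- *Self-report (7.2.1, On-site Medical Observation).* On day 0 participants are told to volunteer accompanying medication, with no end date. This is a real route, but a passive one.
- *Monthly calls (7.3.1, item 6).* "SAEs and AESIs are observed from the first dose to 12 months after the full course of vaccination via monthly telephone follow-up calls". The stated subject is SAEs and AESIs; staff are not told to ask about vaccines.
- *Diary card.* It is back with the site by day 14 (Schedule note 4) or day 28 (7.2.1), long before month 6.
- *Withdrawal criteria (5.1.3) and violation list (7.8.1).* Both name investigational vaccines only, although the violation list is open-ended.
- *Deviation list (7.8.2).* Too short an interval to another vaccine is a deviation, but no question is scheduled to detect it.
- *Monitoring and source files (11.2, 11.8).* Concomitant medication is to be checked and filed; no question to the participant at month 9 or 12 follows from that.

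None of these schedules a question about medication or vaccines after month 6.

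**5. Effect on the comparison.** The protocol gives no uptake, no response to an outside dose and no expected difference at month 9 or 12, so no size can be computed. The direction is also open. Let *d* be the log10 difference between arms and *p* the share vaccinated outside the trial:

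- If the same share *p* in each arm moves to a common titre level, the difference becomes (1 − *p*) × *d*, which is attenuated.
- If the same share in each arm rises by the same factor *f*, each GMT is multiplied by *f*^*p*. The ratio is unchanged and only the GMTs and titre proportions are inflated.
- If the shares differ (*p*T in the test arm, *p*C in the control arm) with the same factor *f*, the ratio is multiplied by *f*^(*p*T − *p*C), which can go either way.

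**The case against.** The strongest reply is that recording does not end at month 6. Participants have a standing instruction to report medication, the eCRF duty in 7.6 has no end date, and a missing tick does not cancel that duty. This stands in part: capture after month 6 is passive rather than absent. A reader might infer that a late vaccine could not be detected at all; the self-report instruction in 7.2.1 rules that out.

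A reader might also infer from the blank cells in "Telephone follow-up after vaccination" that the site has no contact with participants after V11. The documents do not support this. V12 and V13 are blood-draw visits, V4 and V6 are blood-draw visits with the same blank, and 7.3.1 requires monthly calls to month 12.

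It can be said, too, that the missing end date in 7.6 is only silence. The section opens with a 0-28 day duty and speaks of an observation period that it does not define, so this may be vagueness rather than contradiction. That is fair. The point needs no outright conflict: the stated purpose covers drug use during the trial, and the schedule does not serve that purpose at months 9 and 12.

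Finally, the Immunogenicity Persistence Set in 10.2 does not say how to treat samples taken after an outside vaccine. A reader might count this as a further defect. It is not one here, because what counts as valid antibody data can properly be settled in a SAP.

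**Conclusion.** The point holds as a gap in scheduled data collection. At 2 of the 4 persistence visits, over about 180 days (150 to 210 with the windows), a licensed COVID-19 vaccine would be captured only by self-report or by chance. The 9- and 12-month results for secondary endpoint 3 may therefore include samples taken after an unrecorded vaccine. This rests on the tick pattern being as printed and on the visit days in 7.4.

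A reader might infer that the late between-arm comparison is biased, or biased toward no difference. The documents do not show that: uptake and response are not given, and under an equal fold rise with equal uptake the ratio does not move. The day-14 primary endpoint, the day-28 results and the sample size of 516 are untouched, and recording is scheduled at months 3 and 6. The severity is minor to moderate and confined to a secondary endpoint. The reason to act is that the correction is cheap and that vaccination dates not collected cannot be restored by the analysis.

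**What to change.** 1. Tick Concomitant Medication at V12 and V13 in the Schedule of Events.
2. At V8, V11, V12 and V13, ask each participant about any non-study COVID-19 vaccine and its date, and enter the answer in the eCRF.
3. Reword the rule in 7.6: *No COVID-19 vaccine other than the trial dose through month 12; other non-emergency vaccines are allowed from day 15.*
4. With the dates in hand, report a sensitivity analysis of persistence that excludes samples taken after such a vaccine, beside the analysis of all samples. Its details can be left to the SAP.

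**Cost.** Two ticks, one eCRF question, one sentence and one additional analysis. No visits or samples are added, because blood is already drawn at V12 and V13. The drawback is that persistence data are not imputed (10.7), so the sensitivity analysis is complete-case and may itself be selective. It should therefore accompany the all-samples analysis, not replace it.

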**CONFIDENTIAL**

**Medication Record:** To understand the influence of drug use during the trial on vaccine safety and immunogenicity, and to collect adverse events that may be related to vaccination without omission, investigators should instruct the guardians of the participants to record the medical treatment and medication in diary cards as much as possible and assist in collecting the hospitalization medication records of the participants during the observation period. When SAE occurs, copies of corresponding medical records and medication records should be collected and kept. The all study additional drugs need to be transcribed into the electronic case report form (eCRF), such as but not limited to:

1. Hormone/steroid drugs and other immunosuppressants.
2. Antiallergic Drugs
3. Antipyretics/analgesics/NSAIDs
4. Prophylactic Vaccines
5. Therapeutical Medical Products
6. Antibiotics
7. Antiviral Drugs
8. Chinese Patent Drugs

CONFIDENTIAL

### 7.7 Criteria for Suspension or Early Termination

- The number of participants with adverse reactions of severity Grade 3 or above exceeds 15% of the participants vaccinated in this subgroup;
- One case of Grade 4 adverse reaction related to vaccination or SUSAR;

